#### *Process by which Adverse Events Will be Managed and Reported:*

As outlined above, we will continuously monitor adverse event rates in all participants. [name] will have primary responsibility for reporting Adverse Events, Serious Adverse Events, and Unanticipated Problems to the Augusta University IRB, the study's Safety Monitor, and the NIH/NIDDK as required. If [name] is unable to fulfill these duties, PI [name] will have secondary responsibility for reporting.

a. *Describe what data are reviewed, including safety data, untoward events, and efficacy data.*

As described above, adverse events reports and infant growth will be monitored.

b. *Describe how the safety information will be collected (e.g., with case report forms, at study visits, by telephone calls with participants).*

We plan to collect adverse event data from the intervention and control groups as they occur using adverse event reports.

c. *Describe the frequency of data collection, including when safety data collection starts.*

The Project Coordinator will plot each child's growth on the CDC charts within one week following study visits to allow for identification of potentially concerning growth patterns. [name] will review the growth charts of active study participants at least twice monthly to allow for close monitoring and contact mothers as necessary. Safety reports will be sent to [name], the PIs, and the Safety Monitor ([name]) twice per year. The Project Coordinator will be responsible for assembling the data and producing these reports in conjunction with the study statistical team, as well as assuring that all parties obtain copies of these reports.

d. *Describe who will review the data.*

Data will be reviewed as described above by Drs. [name] and [name], by the Project Coordinator, and by the Safety Monitor. The Safety Monitor for the study will be [name]., Associate Professor of Pediatrics at Augusta University. [name] is Division Chief of the Department of General Pediatrics at Augusta University and has the necessary expertise and experience to serve as an objective Safety Monitor for this trial. [name] is not involved in or affiliated with the grant in any capacity other than in his role as Safety Monitor. He has agreed to serve as the Safety Monitor for this project.

e. *Describe the frequency or periodicity of review of cumulative data.*

We will continuously monitor adverse event rates in all participants. PI [name] will have primary responsibility for reporting Adverse Events, Serious Adverse Events, and Unanticipated Problems to the AU IRB, the study's DSMB, and the NIH/NIDDK as required. PI [name] will have secondary responsibility for reporting.

Safety reports will be sent to the study statistician, the PIs, and the Safety Monitor twice yearly. The Project Coordinator will be responsible for assembling the data and producing these reports in conjunction with the study statistical team, as well as assuring that all parties obtain copies of these reports.

f. *Describe any conditions that trigger an immediate suspension of the research.*

#### **Stopping Rules:**

As outlined above, we will continuously monitor adverse event rates in all participants. The study investigators, together with the Safety Monitor, will alert the IRB and the NIH/NIDDK if a greater

than or equal to 20% adverse event rate potentially due to study interventions should occur in the treatment group.

Any participant with a serious adverse event related to the study interventions will be discontinued from the study. Should insufficient weight gain be detected and the cause of this weight gain is related or potentially related to the study interventions as determined by Drs. [name] and [name], the participant will be discontinued from the study. Other non-minor concurrent illnesses or major changes in the family social environment would also lead to discontinuation as determined by the investigators.

As described in detail above, we will closely monitor rates of insufficient growth for individual infants and by study treatment group. In addition to individual level monitoring, the study statistician will analyze rates of insufficient growth by treatment group on a biannual basis if necessary. If there are significantly more children with inadequate growth in the intervention group at any point, these data will be presented to the Augusta University and UGA IRBs, the study's Safety Monitor, and the NIH/NIDDK so that a decision can be jointly made as to whether the trial needs to be suspended.

We acknowledge that there are other situations that could occur that might warrant stopping the trial, and these concerns will be discussed by [name], [name], and the Safety Monitor as needed.

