### *Adverse Events Related or Potentially Related to the Study Interventions:*

It is theoretically possible that behavioral interventions designed to prevent rapid weight gain during infancy could result in underfeeding by parents and insufficient growth. The NIH-funded studies that serve as the foundation for the current project did not find an association between study interventions and these adverse events. While the results of these previous projects are reassuring, weight status and growth will be closely monitored and evaluated at frequent intervals in the current project in order to monitor the study intervention for potential adverse events. In the current study, there are several ways a potential adverse event related to growth will be identified:

1. Weight-for-age below the 5th percentile using current CDC growth charts, based on WHO data from birth to 2 years.

2. Downward crossing of two major percentile lines on the WHO weight-for-age growth chart statistically evaluated as equal to or greater than a -0.67 Z-score change in order to provide a consistent measure across subjects.

Recognizing that growth monitoring is typically performed at all regularly scheduled primary care appointments, we will also ask mothers if their infant's PCP expressed concerns that the infant is demonstrating insufficient weight gain. In turn, the study team will determine if the infant meets one of these screening criteria above when assessed at study visits at 1 week, 3 weeks, 8 weeks, or 16 weeks.

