During each study visit, home visit staff will assess weight. Within one week of the visit, the Project Coordinator will plot each child's growth on the CDC growth charts to allow for identification of potentially concerning growth patterns. [name] will be immediately alerted by the Project Coordinator to any concerning patterns (i.e., weight-for-age below the 5th percentile or downward crossing of two major percentile lines). After each child is closely evaluated, [name] will then contact the mothers by phone when necessary (i.e., when there is a potential adverse event related to infant growth), to discuss their infants' growth and whether a visit with the infant's primary care provider is necessary. If [name] is unable to reach the infant's mother and/or if the mother requests it, [name] will contact the infant's primary care provider directly. [name] will document these calls as they occur as a research note. [name] will review growth charts of all active study participants at least twice monthly.

For any individual child that meets initial screening criteria for growth concerns, numerous factors will be considered in determining whether the child's growth is problematic and/or related to study interventions. Examples of such factors include genetic potential based upon parental size, the participant's linear growth, feeding mode (breast milk vs. formula), and interval illnesses.

The study's informed consent document will include information indicating that the study team will communicate with the participant's PCP if necessary; all infants are required to have a PCP prior to discharge from the hospital and are expected to receive normal medical care (e.g., well-baby visits) throughout the study as is typical for infants. Doing so will allow for open lines of communication between the study team and the PCPs in the event of concerns related to growth. If either the primary care provider or the study investigators believe that it is possible that these growth patterns are a negative result from study participation, the child will be withdrawn from the study.

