#### *Expected Rates for Failing Screening Criteria for Adverse Events Potentially Related to Study Interventions:*

Using standard population distributions, it is expected that 5% of children will be below the 5th percentile on the weight-for-age growth chart. For downward crossing of two major centile lines, it is expected that this will occur with some frequency given the well-established phenomenon of regression to the mean, which suggests that infants born at the higher percentiles have a higher probability of moving downward to the population mean. The results of our pilot study suggest that 15% of participants may experience this, and that will serve as the cut-off alarm value for this study. Combined, these two screening criteria allow for up to a 20% adverse event rate for those events related or potentially related to the study interventions.

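### The 20% growth alert in the treatment arm sits at the top of the rate the plan expects without harm, and the between-arm analysis that would make it interpretable is optional (minor)

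*Supplement*

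**What the plan says.** All references are to the latest protocol version in the Supplement, Section 8 (Data and Safety Monitoring Plan).

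- **Screening criteria.** The subsection on adverse events related or potentially related to the interventions lists two: weight-for-age below the 5th percentile, and a downward centile crossing evaluated as a z-score change of -0.67. The team checks whether an infant "meets one of these screening criteria above when assessed at study visits at 1 week, 3 weeks, 8 weeks, or 16 weeks". A case review follows: "For any individual child that meets initial screening criteria for growth concerns, numerous factors will be considered in determining whether" growth is a problem or is related to the intervention.
- **Expected rates.** The next subsection takes 5% for the first criterion from population distributions. For the second it cites regression to the mean and says pilot results "suggest that 15% of participants may experience this, and that will serve as the cut-off alarm value for this study". It then concludes: "Combined, these two screening criteria allow for up to a 20% adverse event rate for those events related or potentially related to the study interventions".
- **Alert.** Stopping Rules alerts the IRB and NIH/NIDDK if a rate greater "than or equal to 20% adverse event rate potentially due to study interventions should occur in the treatment group".
- **Between-arm rule.** The same subsection says that "If there are significantly more children with inadequate growth in the intervention group at any point", the data go to the IRBs, the Safety Monitor and NIH/NIDDK for a joint decision on suspension. The analysis behind it is described as follows: "the study statistician will analyze rates of insufficient growth by treatment group on a biannual basis if necessary". No test or level is named.
- **Reporting.** "Safety reports will be sent to the study statistician, the PIs, and the Safety Monitor twice yearly".

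**The concern.** Neither component of the 20% is attributed to harm: one is a property of the reference chart, the other is ascribed to regression to the mean. The alert line is thus the ceiling of the plan's own no-harm expectation. It has no allowance for chance, no minimum number of infants and no control-arm figure attached, although rates are watched continuously.

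Insufficient growth is the harm this monitoring is built around. If the treatment arm reaches 20%, the recipients must judge whether the programme is causing underfeeding or whether infants are behaving as predicted. The single-arm rate cannot tell them. The control arm can, because both arms are weighed and screened on the same schedule, yet the scheduled comparison is the part left to discretion.

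**Working it through.** **1. The plan's 20%.** 0.05 + 0.15 = 0.20, which reproduces the stated figure. It assumes that no infant fails both criteria. If the criteria are independent, the rate is 1 - 0.95 × 0.85 = 0.1925. If every infant below the 5th percentile also crosses downward, it is 0.15. The plan's inputs therefore imply 15% to 20% without harm.

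**2. When the rate is looked at.** Section 4 plans 50, 125, 125 and 75 dyads in years 1 to 4. Assuming equal allocation and even accrual within years, cumulative treatment-arm numbers at half-yearly looks are about 12, 25, 56, 87, 119, 150, 169 and 187. The six looks from 56 infants onward are the main case.

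**3. Chance of an alert with no harm, all screening failures counted.** At each look the alert needs at least 20% of n, that is 12, 18, 24, 30, 34 and 38 infants at the six looks. A single look is the binomial tail P(X ≥ 38 | 187, p). Repeated looks use an exact recursion on the cumulative count.

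| True rate | One final look (187) | Six looks from 56 | All eight looks |
|---|---|---|---|
| 15% (full overlap) | 0.03 | 0.19 | 0.45 |
| 17.5% | 0.18 | 0.44 | 0.65 |
| 19.25% (independent) | 0.38 | 0.64 | 0.78 |
| 20% (no overlap) | 0.49 | 0.72 | 0.83 |

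Allowing for the 16-week follow-up lag leaves the six-look figures at 0.19 (15%) and 0.72 (20%). Allowing for 10% attrition gives 0.26 and 0.75.

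**4. How much an alert tells the reader.** Over six looks the alert fires with probability 1.00 if the true rate is 30%, and 0.98 if it is 25%. For a 10-point rise, an alert multiplies the odds of harm by:

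- 1.00 / 0.72 = 1.4 from a 20% background;
- 0.978 / 0.189 = 5.2 from a 15% background.

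The alert is sensitive. How specific it is depends on a background rate that is not known in advance.

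**5. The between-arm comparison, run routinely.** Pooled two-proportion z-test, one-sided 5% at each of the six looks, 400,000 simulated trials:

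| Treatment v control | Chance of a signal |
|---|---|
| 15% v 15% | 0.125 |
| 20% v 20% | 0.125 |
| 25% v 20% | 0.44 |
| 30% v 20% | 0.81 |
| 25% v 15% | 0.85 |
| 40% v 20% | 1.00 |

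For a 10-point rise, a signal multiplies the odds of harm by 0.806 / 0.125 = 6.4 from a 20% background and 0.852 / 0.126 = 6.8 from 15%. Unlike the single-arm alert, its value hardly depends on the background.

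**The case against.** **It only notifies.** This stands. Reaching 20% stops nothing, and a false alert costs a report. For infants, a tripwire that fires readily is a defensible choice. A reader might infer from the subsection title that crossing 20% halts the trial, but the text does not say so.

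**Comparative monitoring exists.** This also stands. A reader might infer that the plan never uses the control arm. In fact Stopping Rules commits to watching growth by treatment group, and its between-arm rule leads to the suspension decision. Nothing suggests that the recipients of an alert would be refused control data. What remains is that the statistician's scheduled analysis is conditional and has no stated test or level.

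**The numerator is clear enough.** Largely so. The 20% is derived from screening failures under headings that call them potentially related events, so counting all failures is the natural reading. A reader might instead infer that only infants judged related after case review count, in which case 20% could miss a real rise. The alert sentence does not exclude that, but the derivation points the other way, and the plan gives no share judged related from which to size the effect.

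**The background could be well above 20%.** A reader might infer this from four screening visits against a single-visit 5%, and from the eligibility of late pre-term infants. The documents do not support a large excess. A visit-to-visit correlation as low as 0.7 would raise the first criterion noticeably, but would also imply that about 60% of infants cross downward, not 15%. Correlations that roughly reproduce 15% (about 0.93 to 0.95) give about 22%, and that is itself an assumption. No late pre-term proportion is stated.

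**A higher line loses sensitivity.** Correct. A single-arm table with a 2.5% margin per look (18 of 56 rising to 49 of 187) cuts the six-look false-alert chance at 20% to 0.056, but detection of a true 25% falls from 0.98 to 0.47. That is a matter of preference and is not pressed here.

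**Conclusion.** The concern holds as a minor point. If all screening failures count, the 20% line cannot reliably separate harm from the background the plan itself predicts. The chance of a harmless alert over six looks runs from 0.19 at a 15% background, through 0.64 at 19.25%, to 0.72 at 20%. At one final look it runs from 0.03 through 0.38 to 0.49. These figures assume equal allocation, independent infants and half-yearly looks from about 56 infants per arm.

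The documents do not show that harm would go undetected, that the trial would stop wrongly, or that single infants are unprotected. Individual growth review and withdrawal are unaffected. The weakness is narrow: the signal most likely to fire is the less informative one, and the more informative one is not firmly scheduled.

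**What to change.** 1. In Stopping Rules, delete the last two words of "the study statistician will analyze rates of insufficient growth by treatment group on a biannual basis if necessary" and run the comparison at every twice-yearly safety report.
2. Define what is compared: infants in each arm who first meet either screening criterion after the 1-week visit. Randomisation takes place at that visit and the first programme session is at 3 weeks, so a failure already present at 1 week cannot be an effect of the sessions.
3. State the test and level. One-sided 5% per report, starting at about 50 infants per arm, would serve: about 0.12 chance of a false signal over six reports and 0.81 detection of 30% against 20%. A stricter one-sided 2.5% gives about 0.07 and 0.70.
4. Keep the 20% line as a sensitive tripwire if wanted, but always report the control-arm rate beside it. A higher single-arm table is optional.

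The cost is a few sentences in the monitoring plan, a little more analysis at each report, and an occasional false between-arm signal to be explained. No new data are needed: both arms are already weighed at each visit, and the reports already go out twice a year. The comparison will often miss small rises (0.44 for 25% against 20%), which is a reason to keep the tripwire alongside it.

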## 9. Withdrawal of Subjects

☐ N/A

|                                                                                                                                                                                                                                                                                                                                                                                                                                                                                                                                                                                                                                                                                                                                                                     |                                     |
|---------------------------------------------------------------------------------------------------------------------------------------------------------------------------------------------------------------------------------------------------------------------------------------------------------------------------------------------------------------------------------------------------------------------------------------------------------------------------------------------------------------------------------------------------------------------------------------------------------------------------------------------------------------------------------------------------------------------------------------------------------------------|-------------------------------------|
| 
a. If applicable, describe anticipated circumstances under which subjects will be withdrawn from the research without their consent.
 
Any participant with a physician-diagnosed serious adverse event related to the study interventions will be discontinued from the study. Should insufficient weight gain be detected and the cause of this weight gain is potentially related to the study interventions as determined by the PIs after consultation with the participant's primary care provider, the participant will be discontinued from the study. Other non-minor concurrent illnesses or major changes in the family social environment would also lead to discontinuation as determined by the investigators.
                     | 
 N/A
 |
| 
b. If applicable, describe any procedures for orderly termination.
 
In the event that a subject is withdrawn from the research without their consent (whether due to unforeseen change in meeting inclusion criteria or an adverse event), all contact with subject will be ceased. Subjects will receive monetary compensation only for those appointments and study requirements met until the date of withdrawal. Any materials provided (bassinet, intervention materials) as part of the study procedures will remain with the subject. Only if agreed to at the time of consent, data collected for that subject dyad until the date of withdrawal will remain part of the study data and included in researcher analysis where possible.
 | 
 N/A
 |
| 
c. If applicable, describe procedures that will be followed when subjects withdraw from the research, including partial withdrawal from procedures with continued data collection.
 
In the event that subjects withdraw from the research, all contact with subject will be ceased. Subjects will receive monetary compensation only for those appointments and study requirements met until the date of withdrawal. Any materials provided (bassinet, intervention materials) as part of the study procedures will remain with the subject. Only if
                                                                                                                                                                                            | 
 N/A
 |

|                                                                                                                                                                                            |  |
|--------------------------------------------------------------------------------------------------------------------------------------------------------------------------------------------|--|
| agreed to at the time of consent, data collected for that subject dyad until the date of withdrawal will remain part of the study data and included in researcher analysis where possible. |  |
|--------------------------------------------------------------------------------------------------------------------------------------------------------------------------------------------|--|

## 10. Risks to Subjects

|                                                                                                                                                                                                                                                                                                                                                                                                                                                                                                                                                                                                                                                                                    |       |
|------------------------------------------------------------------------------------------------------------------------------------------------------------------------------------------------------------------------------------------------------------------------------------------------------------------------------------------------------------------------------------------------------------------------------------------------------------------------------------------------------------------------------------------------------------------------------------------------------------------------------------------------------------------------------------|-------|
| 
a. List the reasonably foreseeable risks.
 
Potential risks. All participants will continue to receive their standard care from their medical providers. Our previous research found no increased risk of adverse events, or specifically failure to thrive, among those infants randomized to receive the multi-component prevention program. Given that the proposed study is focused on infant sleep and soothing, rather than focused on feeding, and is of significantly shorter duration than our previous multi-component trials, there is extremely minimal risk of insufficient weight gain and/or failure to thrive in the experimental group.
 |       |
| b. If applicable, describe any costs that subjects may be responsible for because of participation in the research.                                                                                                                                                                                                                                                                                                                                                                                                                                                                                                                                                         | ■ N/A |
| c. If applicable, describe risks to others who are not subjects.                                                                                                                                                                                                                                                                                                                                                                                                                                                                                                                                                                                                            | ■ N/A |

